### Study population

All adult PWE attending the neurology clinics at Mulago and Mbarara hospitals during the study period who or their caregivers will be approached. All participants and their legal guardians will provide written informed consent. All consecutive patients who came either for follow-up or as new referrals with a confirmed diagnosis of epilepsy will be screened for inclusion in the study. We will include those who meet the following inclusion criteria: 1. Participants will have a clinical diagnosis of epilepsy documented with at least two outpatient visits; 2. aged more than 18 years; 3. provide written informed consent by the study participant or immediate caregiver/legal guardian; 4. Ability to participate in study procedures, 5. having had at least 1 seizure in the past 6 months; 6. Owning a mobile phone either by the PWE or immediate caregiver.

We will exclude those 1. Diagnosed with dementia, 2. Participants who are pregnant (given the likely need for different and more intensive treatments among pregnant PWE, may affect their ability to participate in the SMART-U sessions regularly and those unable to participate in study procedures.

### Study procedures

#### Randomisation:

Participants will be randomly assigned in a ratio of 1:1 basis to receive either SMART-U (N = 94) or eTAU (N = 94) using block randomisation. Block randomisation with a random block size of 4 to 8 consecutive patients will be performed to ensure that equal numbers of SMART and ETAU patients occur within strata and are balanced. The randomisation list will be computer-generated by staff from the CWRU Neurological and Behavioural Outcomes Centre Biostatistical Core who are not part of the study staff.

#### SMART-U Intervention group:

The SMART-U self-management approach of the intervention uses nurses and peer educator dyads (PEDs) made up of patients and their care partners to deliver the intervention together. SMART-U begins with a 30–60-minute orientation session where the nurse and PED meet with the patient and their care partner. This is followed by 6 weekly, one-hour group sessions with 6–8 patients and their care partners. Topics covered are noted in Table 1 and are typically delivered over a period of 10–12 weeks. All SMART-U participants continue to receive treatment with their regular medical care providers.

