### Study design

This prospective non-inferiority randomised clinical trial will be conducted at Mulago and Mbarara hospitals. Participants will be adults who meet the inclusion criteria from the epilepsy clinics at Mulago and Mbarara who will be approached to participate in the study and enrolled.

The estimated sample size for the study is 188 people with epilepsy, allowing for 20% attrition or loss by missing data, reducing the final sample to a minimum of N = 150 participants.

Based on a power analysis using G*Power 3.1.9.2121 for a 2 group by 3 time points (baseline, 13-week and 24-week follow-up) repeated measures analysis of variance (RMANOVA) with an alpha of 0.05, a power of. 80, for a sample of 150 we will be able to detect a small standardised effect size of 0.10 for the within-time effect, within the time-by-group interaction effect and a small to moderate standardised effect of 0.19 for the between-group effect.

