#### Control arm-Enhanced Treatment as Usual (eTAU) group:

Individuals randomised to eTAU will continue in their usual care supplemented by written materials on epilepsy in their preferred language and tailored to the reading level of most patients at the clinic. To control for the same number of patient contacts as SMART-U, the nurse in eTAU will follow up with participants with a series of 8 brief phone calls spaced out over the course of 6 months (approximately every 2 weeks during months 1 and 2, then approximately monthly thereafter).

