#### Data analysis and Data management:

The investigators at each study site will oversee data input and quality and, working with the study statistician and epidemiologist, will oversee the quantitative data analytic procedures. The CWRU data management and statistics team will also provide data management consultation as appropriate. Rigorous development of data collection forms and staff training on properly completing and checking data collection forms will reduce errors at the point of collection. Additional data management practices before and after entry into the RedCap database will identify potential problems or outlying values and catch other errors on data collection forms. Data management staff will be responsible for tracking forms entered and performing routine data checks. Analytic data sets will be prepared using SAS 9.4

Repeated Measure Analysis of Variance. The primary outcomes of interest are quality of life (QOL) and cumulative seizure frequency. Three different analytic strategies will be used to assess AIM 1. Cumulative seizure frequency will be assessed with independent samples t-tests and linear regressions, while QOL and the secondary outcomes will be examined using repeated measures analysis of variance (RMANOVA). We will examine 2 different sets of RMANOVAs.

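### SMART-U is delivered in groups of 6–8, but the named tests and power model have no group term; if outcomes correlate within groups, the false-positive rate exceeds 5%

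*Protocol article*

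**What the plan says.** **Allocation.** Under Randomisation, individuals are allocated: "Participants will be randomly assigned in a ratio of 1:1 basis to receive either SMART-U (N = 94) or eTAU (N = 94").

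**Delivery.** Under SMART-U Intervention group, the programme "uses nurses and peer educator dyads (PEDs) made up of patients and their care partners to deliver the intervention together", and after an orientation session it runs as "group sessions with 6–8 patients and their care partners". Under the control arm heading, eTAU participants receive written materials and, from a nurse, "a series of 8 brief phone calls spaced out over the course of 6 months". One arm is therefore treated in groups and the other individually.

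**Analysis.** Under Data analysis and Data management: "Cumulative seizure frequency will be assessed with independent samples t-tests and linear regressions, while QOL and the secondary outcomes will be examined using repeated measures". The last method is RMANOVA.

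**Power.** Under Study design, the calculation is "for a 2 group by 3 time points (baseline, 13-week and 24-week follow-up) repeated measures analysis of variance (RMANOVA"). Its inputs are 5% alpha, 80% power and 150 analysed participants. The detectable standardised effect is put at 0.10 for the tests that involve time; for the comparison of arms the article gives "a small to moderate standardised effect of 0.19 for the between-group effect".

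The article nowhere mentions a therapy-group effect, an ICC, a design effect or cluster-robust standard errors.

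**The concern.** This is a partially nested design. Members of one SMART-U group share a nurse, a peer educator dyad and the same discussions, and Table 1 lists role play, social support and group process among the contents. Their outcomes may therefore resemble each other more than those of participants in different groups. No such grouping exists in eTAU.

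An independent-samples t-test and an ordinary linear regression treat each participant as a separate piece of information. RMANOVA allows for correlation between visits of one person, but not between people in the same group. With positive within-group correlation, the SMART-U mean varies more than these methods assume. The standard error of the difference is then too small, and chance differences in either direction are declared significant too often. The 150 analysed participants also carry less information than the power statement assumes. Both co-primary outcomes are analysed by methods of this kind.

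**Working it through.** **Inputs from the protocol article.** 94 randomised per arm; groups of 6–8; 20% attrition; 150 analysed, so 75 per arm; alpha 0.05; power 0.80; between-group effect f = 0.19.

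**Assumed, because not stated.** ICC of 0.01, 0.05 and 0.10; correlation of 0.5 between repeated measures and sphericity for the RMANOVA power; two-sided testing.

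**1. The plan's own figures.**
- Enrolment: 150/(1 − 0.20) = 187.5, rounded up to 188. This matches.
- Between-group effect: noncentrality = f²·N·3/(1 + 2·0.5) = 0.19² × 150 × 3/2 = 8.12. With 1 and 148 degrees of freedom, power is 80.8% and the detectable f at 80% is 0.188. This agrees with the stated 0.19, under a model of independent participants.

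**2. Number and size of groups.**
- Groups formed: 94/8 = 11.75 to 94/6 = 15.7, so about 12–16.
- If the 20% loss spreads evenly over groups, analysed members per group are m = 0.8 × 6 = 4.8 to 0.8 × 8 = 6.4.

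**3. Effect of clustering in one arm.**
- Design effect in SMART-U: DE = 1 + (m − 1)·ICC.
- Variance ratio for the difference in means: V = (DE + 1)/2, since eTAU has a design effect of 1.
- Actual two-sided alpha of the unadjusted test: 2·[1 − Φ(1.96/√V)].
- Effective N: 150/V. Detectable f: 0.188·√V.

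Example, m = 6.4 and ICC 0.05: DE = 1 + 5.4 × 0.05 = 1.27; V = 1.135; √V = 1.065; 1.96/1.065 = 1.840; alpha = 6.6%; effective N = 150/1.135 = 132; detectable f = 0.188 × 1.065 = 0.200.

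| ICC | V (m = 4.8 to 6.4) | Actual alpha | Effective N | Power for f = 0.19, clustering allowed for | Detectable f |
|---|---|---|---|---|---|
| 0.01 | 1.019–1.027 | 5.2–5.3% | 146–147 | about 80% | 0.190–0.191 |
| 0.05 | 1.095–1.135 | 6.1–6.6% | 132–137 | 76–77% | 0.197–0.200 |
| 0.10 | 1.190–1.270 | 7.2–8.2% | 118–126 | 71–74% | 0.205–0.212 |

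The power column uses the step 1 formula with effective N in place of 150. It ignores the further loss of degrees of freedom from having only 12–16 groups.

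**4. Check by simulation.** Forming groups from 94 participants, dropping at random to 75 and applying the t-test to normal outcomes (40,000 runs per setting) gave about 6.2–6.6% at ICC 0.05 and 7.3% to about 8.4% at ICC 0.10.

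**5. Upper bound.** If analysed groups stay at 6–8, the same formula gives 6.5–7.1% at ICC 0.05 (m = 8: V = 1.175) and 8.0–9.2% at ICC 0.10 (m = 8: V = 1.35).

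**The case against.** **No ICC is stated, so inflation is not established.** This stands as a limit. A reader might infer that the false-positive rate certainly exceeds 5%. The article does not support that: at ICC 0 there is no inflation, and at ICC 0.01 it is about 0.2–0.3 percentage points, which is negligible. The claim is conditional on positive correlation within groups.

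**Only the t-test was calculated.** A reader might carry these percentages over to QOL and every secondary outcome. The direction is the same for between-group comparisons in the RMANOVAs, but ICCs can differ by outcome, and seizure counts are unlikely to be normal. The size is not shown for those analyses.

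**The article is condensed and the SAP is not shown.** The covariates of the regressions and the two sets of RMANOVAs are not described, so a group term could be added elsewhere. This weakens the point for the regressions. It does not remove it: the article names independent-samples t-tests and gives a power model based on independent participants. A SAP with a group term would have to depart from those t-tests, and the published power statement would still ignore clustering.

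**Group membership may well be recorded.** A reader might infer that it is not. The article does not say either way, so no such failing is claimed.

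**Conclusion.** The point holds in conditional form. The article fixes tests and a power model without a group term for a design in which one arm is treated in groups. Any positive within-group correlation makes the standard errors too small. For the t-test, with attrition spread over the groups, the nominal 5% becomes about 6.1–6.6% at ICC 0.05 and 7.2–8.4% at ICC 0.10. If attrition does not thin the groups, these rise to at most 7.1% and 9.2%.

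The loss of power is modest. The planned 80% for f = 0.19 is essentially kept at ICC 0.01, and falls to about 76–77% at ICC 0.05 and 71–74% at ICC 0.10 once the analysis allows for clustering. A reader might conclude that the trial must be enlarged; the documents give no ICC that would justify this. The results rest on the assumed ICC range, even attrition, and a correlation of 0.5 between repeated measures. The analysis should be corrected, but the design itself is not invalid.

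**What to change.** 1. **Data.** Keep the session-group identifier for every SMART-U participant in the analysis data set.
2. **Analysis.** Analyse by randomised arm and allocated group, whatever the attendance, with a partially nested mixed model: random group intercept in SMART-U only, eTAU participants as singletons, arm-specific residual variance, and Satterthwaite or Kenward-Roger degrees of freedom because there are only about 12–16 groups. Use this for both primary outcomes and for the secondary outcomes, with the repeated visits modelled within participant where they are analysed.
3. **Power statement.** Under Study design, restate the detectable between-group effect on the f scale over an assumed ICC range, for example 0.01–0.10. With N = 188 enrolled and 150 analysed, it moves from about 0.19 to about 0.19–0.21. Restate the time-by-group figure on the same basis.

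**Cost.** One identifier field and revised model wording. Intervals become slightly wider and the stated detectable effect slightly larger. Enrolment and delivery do not change. If the ICC proves close to zero, little precision is lost.

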#### Control arm-Enhanced Treatment as Usual (eTAU) group:

Individuals randomised to eTAU will continue in their usual care supplemented by written materials on epilepsy in their preferred language and tailored to the reading level of most patients at the clinic. To control for the same number of patient contacts as SMART-U, the nurse in eTAU will follow up with participants with a series of 8 brief phone calls spaced out over the course of 6 months (approximately every 2 weeks during months 1 and 2, then approximately monthly thereafter).

#### SMS seizure monitoring and support:

During the 24-week duration of the trial, both SMART-U and eTAU participants will receive/use SMS to monitor/report seizure occurrence and duration. Participants will receive an automated weekly survey via SMS asking if they had a seizure in the past week.

#### Feasibility and Fidelity:

Acceptance will be assessed at the end of each series of 8 group sessions with a short self-assessment survey. Following Fraser, fidelity to the SMART-U intervention will be assessed quantitatively and qualitatively. Research staff not involved in the intervention will monitor and score at least 25% of the group sessions, rating each dimension of fidelity on a scale of 1 to 10. The feasibility of texting for both the SMART-U -U and eTAU groups will be assessed by the number of text responses/number of texts sent.

#### Qualitative evaluation:

We will use In-depth interviews on perceived benefits vs. burdens and barriers/facilitators to SMART-U, and eTAU implementation will be conducted at each of the 2 sites. Given the corrosive and persistent nature of stigma on QOL among PWE, input and recommendations on specific strategies regarding ways to potentially mitigate stigma in families and communities will be assessed. Informants will include 20 PWE from SMART-U and 20 PWE from eTAU (total N = 40). We will conduct qualitative interviews to elicit participant perceptions of the intervention at 13-weeks (when SMART-U groups are completed) and again at 24 weeks. For qualitative interviews, this sample size is within the range of recommended sample sizes (i.e., 20–50 individuals).

#### Study outcomes:

The Primary outcome will be Mean change in cumulative past 24-week seizure frequency (24 weeks prior to study baseline compared to the 24-week follow-up) and Mean change from baseline to 24 weeks in QOL. Additional secondary outcomes will include Mental health comorbidity, stigma, epilepsy self-management competency, and other relevant variables, which will be assessed using validated, standardised questionnaires.

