**Methods::**

A total of 188 adult people with epilepsy (PWE) attending the neurology clinics at Mulago and Mbarara hospitals and consent to participate in the study. They will be randomised into intervention versus enhanced treatment control (eTAU) study groups. The intervention group will receive 12-week “intensive” educational sessions and a 12-week remotely accessed telephone follow-up stage. The controls will continue in their usual care supplemented by written materials on epilepsy in their preferred language and tailored to the reading level of most patients at the clinic. SMART-U consists of 2 main components: a 12-week “intensive” group format stage and a 12-week remotely accessed telephone follow-up stage. SMART-U will be assessed for acceptability, fidelity, and efficacy compared to eTAU. The primary study outcome is the mean change in cumulative past 24-week seizure frequency (24 weeks prior to the study baseline compared to the 24-week follow-up). Seizure frequency will be via self-report with corroboration by family/support system informants whenever possible. Participants will self-report their seizure frequency (numeric count) that they experienced between baseline and 13 weeks and again between 13 and 24 weeks and the mean change from baseline to 24 weeks in QOL.

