### Study objectives

To assess the efficacy of SMART- U vs. eTAU in a prospective randomised controlled trial.

We hypothesised that individuals randomised to SMART-U will have significantly improved QOL with fewer seizures, have greater improvement in depression and functional status compared to eTAU.

To use short message service (SMS) delivered via mobile phone text to validate patient self-reported seizure occurrence and push epilepsy self-management messaging in a practical/accessible format.To obtain input from stakeholders (patients, family and clinicians) guided by an Integrated Promotion Action on Research Implementation in Health Services (i-PARIHS) framework to help establish sustainable infrastructure that will facilitate future scale-up of SMART in Uganda with epilepsy partners

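### The two halves of the seizure change score are ascertained differently, so within-arm change is not interpretable; define the effect as a between-arm comparison of follow-up counts adjusted for baseline

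*Protocol article*

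**What the plan says.** Under Study outcomes, the protocol article gives the primary seizure outcome as "Mean change in cumulative past 24-week seizure frequency (24 weeks prior to study baseline compared to the 24-week follow-up", next to change in quality of life.

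The Abstract (Methods) says how the count is obtained: "Seizure frequency will be via self-report with corroboration by family/support system informants whenever possible". For follow-up it adds: "Participants will self-report their seizure frequency (numeric count) that they experienced between baseline and 13 weeks and again between 13 and 24 weeks". No such split is described for the 24 weeks before baseline.

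The section on SMS monitoring limits the prompts to the trial period and gives them to both arms: "During the 24-week duration of the trial, both SMART-U and eTAU participants will receive/use SMS to monitor/report seizure occurrence and duration". The content is a yes/no question: "Participants will receive an automated weekly survey via SMS asking if they had a seizure in the past week". Study objectives gives the purpose of the SMS as "to validate patient self-reported seizure occurrence and push epilepsy self-management messaging in a practical/accessible format", so it supports the self-reported count and does not replace it.

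Study objectives states efficacy as SMART-U against eTAU. The data analysis section assigns two-sample t-tests and linear regression to cumulative seizure frequency, and repeated measures ANOVA to quality of life and the secondary measures. It does not say whether the t-tests and regressions act on the change or on the follow-up count.

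**The concern.** A change score is easiest to interpret when both of its halves are measured in the same way. Here the method changes at baseline in two respects: the recall window shortens from 24 weeks to about 13 and 11, and weekly cues begin. Neither depends on missed or late visits; both occur with perfect adherence to the schedule.

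If recall improves after baseline, follow-up counts rise relative to baseline in both arms. A real fall in SMART-U then looks smaller than it is, and an unchanged eTAU arm looks worse. If participants overcount when they look back 24 weeks, the shift runs the other way and both arms appear to improve. Because the outcome is worded as a change from before to after, readers will naturally look at each arm's mean change, and that quantity mixes seizures with ascertainment.

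A second, related matter is precision. A change score subtracts the recalled baseline with a weight of exactly 1, however noisy that recall is.

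**Working it through.** **The plan's own figure.** The sample size reproduces: 150 / (1 − 0.20) = 187.5, rounded up to 188. The point made here does not alter it.

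**Step 1: recall lag (inputs from the Abstract and Study outcomes).** If seizures are spread evenly over each window, the mean gap between a seizure and the interview is
- baseline: 24 / 2 = 12 weeks;
- follow-up: (13 × 6.5 + 11 × 5.5) / 24 = 145 / 24 = 6.04 weeks.

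The weekly SMS is described for none of the 24 baseline weeks and is scheduled throughout the 24 follow-up weeks.

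**Step 2: how far a within-arm change could move (assumed; the documents give no capture rates).** Suppose recall is lost at rate d per week. The captured fraction over a window of W weeks is c(W) = (1 − exp(−dW)) / (dW). Follow-up capture from the windows alone is (13·c(13) + 11·c(11)) / 24. Let k be follow-up capture divided by baseline capture.

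| d per week | Baseline capture | Follow-up capture, windows only | k, windows only | k if follow-up capture is 0.95 |
|---|---|---|---|---|
| 1% | 0.889 | 0.942 | 1.06 | 1.07 |
| 2% | 0.794 | 0.888 | 1.12 | 1.20 |
| 4% | 0.643 | 0.793 | 1.23 | 1.48 |

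The 0.95 in the last column is an assumed capture with prompting. At 1% nearly all of the asymmetry comes from the windows, and at 2% more than half does, so it cannot be put down to the SMS alone.

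Apparent change = k × true ratio − 1. At k = 1.20, no true change appears as +20%, and a true 30% reduction appears as 1.20 × 0.70 − 1 = −16%. If baseline recall overcounts, k falls below 1 and the signs reverse.

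**Step 3: does it reach the randomised contrast?** Simulation, all settings assumed: true mean 10 seizures per 24 weeks, gamma-Poisson counts with shape 1, 75 per arm, no true change, two-sample t-test on the change.

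| Capture before / after baseline (both arms) | Mean change in each arm | Between-arm difference | Rejection rate |
|---|---|---|---|
| 0.8 / 0.9 | about +1.0 | about 0 | 5.3% |
| 0.7 / 0.9 | +2.0 | about 0 | 5.5% |
| 0.5 / 0.9 | about +4.0 | about 0 | 5.2% |
| 1.2 / 0.9 | about −3.0 | about 0 | 4.8% |

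The within-arm change shifts by (after − before) × true mean. The between-arm difference does not. With a true 30% reduction, that difference was −2.70 at capture 0.7 / 0.9 and −2.71 at 0.9 / 0.9, so baseline capture drops out. Only follow-up capture that differs by arm biased the contrast: 0.7 before, then 0.9 against 0.8, gave a difference of about +1.0 and 29% rejection. Nothing in the SMS schedule, which is the same in both arms, implies that.

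**Step 4: change score against covariate.** Same count model, capture 0.79 then 0.95, true 30% reduction, and person-level log-normal error in the recalled baseline (assumed).

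| Log-SD of baseline recall error | Power, t-test on change | Power, follow-up count with baseline as covariate |
|---|---|---|
| 0.3 | 90% | 94% |
| 0.5 | 69% | 84% |
| 0.7 | 49% | 74% |

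The gain comes from noise in the baseline recall, not from the SMS. With no true effect, the t-test on change rejected in 4.5% to 5.1% of runs.

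**The case against.** The strongest reply is that this is a randomised comparison. Efficacy is SMART-U against eTAU, both arms receive the same SMS and the same interviews, and the named tests compare arms. A shift common to both arms cancels. That stands in full: a reader might infer that the primary efficacy test is biased or has an inflated error rate, and neither the documents nor the simulation supports this.

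A reader might also infer that the power statement relies on a time effect in seizures, because it says "we will be able to detect a small standardised effect size of 0.10 for the within-time effect". It does not. That sentence concerns repeated measures ANOVA, which the data analysis section gives to quality of life and the secondary measures. Seizure prompts do not alter how quality of life is ascertained.

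It is also fair to say that the SMS is not the source of the primary count. It asks whether a seizure occurred, and the number comes from interview, so the cue can only aid recall. The shorter windows are at least as clear a cause.

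Finally, the protocol nowhere says that a fall within an arm will be read as efficacy, and the planned regressions may already adjust for baseline in an analysis plan not shown here. Both are true. What remains is that the outcome is worded as a pre-to-post change in both the Abstract and Study outcomes, without stating the between-arm contrast there, and that the data analysis section leaves open which quantity is tested.

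**Conclusion.** The asymmetry is in the text and holds even with perfect adherence. Each arm's mean change in seizure count can move without any change in seizures, by an amount and in a direction that the documents do not fix. The size shown (6% to 23% from the recall windows alone, 7% to 48% with an assumed 0.95 prompted capture) rests entirely on assumed recall loss; overcounting at baseline would reverse it.

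The randomised contrast is not biased in expectation while reporting is alike in both arms, and its type I error stays near 5%. The point is therefore about how the outcome is defined and read, not about the validity of the main test. Adjusting for the recalled baseline, rather than subtracting it, is worth doing anyway: in the assumed settings it gained 4 to 25 percentage points of power.

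**What to change.** - In the Abstract (Methods), Study outcomes and the data analysis section, define the seizure effect as the between-arm comparison of the 24-week follow-up count, with the recalled 24-week baseline count as a covariate, instead of a t-test on the change score.
- State in the same places that within-arm change will not be interpreted as seizure reduction.
- Optionally, ask the 24 weeks before baseline as two dated blocks of about 13 and 11 weeks, with the informant present where possible. This brings the recall windows closer; it does not remove the SMS difference, and the earlier block is still recalled from further back than anything at follow-up.

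The cost is rewording and, for the optional step, one extra line on the baseline questionnaire. No patients or visits are added. The trial would forgo any claim about reduction within an arm, which the protocol does not explicitly make.
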